### 5.1.4 Potential effect modifiers

Stratification into different population:

- Primary vaccination schedule (2 doses): ChAdOx1, BNT162b2
- Age group (18-49,50-64, 65+ years)
- Period of which variant (Delta or Omicron)
- Additional, given that VE may differ between those with multiple underlying medical conditions, that are related to serious COVID-19, we will stratify analyses by COVID-19 risk group when data allow. We will also consider stratifying analyses by vaccine type and calendar time (to reflect different dominant variants present in the country).

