## 2.2 Objectives

By vaccine type, we seek to:

1. Estimate Odds Ratio (OR) against the composite outcome of COVID-19 hospitalisation/death of individuals with booster dose versus individuals without booster dose.
2. Estimate Odds Ratio (OR) against confirmed SARS-CoV-2 infection of individuals with booster dose versus individuals without booster dose.
3. Estimate Rate Ratio (RR) against the composite outcome of COVID-19 hospitalisation/death as a function of time post maximum effect of the booster dose of a COVID-19 vaccine.
4. Estimate RR against the separate outcomes of i) COVID-19 hospitalisation; ii) COVID-19 death as a function of time post maximum effect of the booster dose of a COVID-19 vaccine.
5. Assess if waning of protection from booster dose differs by age group, sex and being in a high-risk COVID-19 group

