# Study Design

## 3.1 Study design

Objectives a) and b) will be evaluated through a test-negative design case-control study

Objective c) and d) open prospective cohort study comparing outcomes amongst vaccinated people for differing lengths of time.

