### 5.1.3 Potential confounders

We will consider adjusting for age, sex, socioeconomic position, geography and where possible, comorbidities. More specifically, we anticipate adjusting for the following confounders in Scotland: age (five-year bands^^[[3]](#footnote-2)^^), sex, socioeconomic position (SEP) measured by quintiles of the Scottish Index of Multiple Deprivation (SIMD) (1 refers to most deprived and 5 refers to least deprived), residential settlement measured by the urban/rural 6 fold classification (1 refers to large urban areas and 6 refers to small remote rural areas), household size, number and types of comorbidities commonly associated with COVID-19 illness (asthma, chronic kidney disease, liver cirrhosis, chronic neurological condition, heart failure, diabetes (type 1 and type 2), dementia, coronary heart disease), risk factors (smoking status, blood pressure, body mass index (BMI)) and Health Board.

In Brazil, we anticipate adjusting for age (five-year bands), sex, the primary reason for vaccination, race/ethnicity and calendar week will be accounted for within the statistical models.

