### 5.1.5 Analytical techniques

We will commence analysis by conducting descriptive analyses to visually inspect trends in vaccination delivery, age-specific COVID-19 hospitalisations and COVID-19 deaths, including by age group and sex. This will include checking the number of people who have received two doses and the length of follow-up available following the second dose by vaccine type. Including plotting Lexis diagram to afford for the correlated structure of the data (Calendar Time/Length of Follow-up)

For the analysis consisting of individuals with at least two doses, we will stratify the cohort based on the month of the second dose of each individual. The vaccination status will be classified as:

- Second dose:
  - <2 weeks
  - 2-9 weeks
  - 10-19 weeks
  - ≥20 weeks without a booster dose [Reference Period]
- Booster dose:
  - <2 week
  - 2-4 weeks
  - 5-8 weeks
  - 9-12 weeks
  - ≥13 weeks

This variable will be used to fit a Poisson regression to obtain rate ratios (RRs) and their 95% confidence intervals (CIs). If we observe overdispersion, we will consider using Negative Binomial regression models or Poisson with robust standard errors. Models will be adjusted for the relevant confounders above, including a set of dummy variables for calendar week.

The models will be fit to a dataset with all events and a random sample, without replacement, of 100 individuals per event (for hospitalisation and death, 10 for positive tests). The sample weights will be calculated to represent the sampling fraction, thus ensuring the correct calculation of the person-years at risk for the whole population.

The primary analysis for the test negative will be on individuals who are symptomatic at the time of test and the date of symptom onset is 0-10 days before the test. We will then establish the number of weeks post-vaccination for the cases and controls calculated as time between sample collection date and vaccine dose. The odds' ratio will be calculated using a logistic regression. Adjusted for: race/ethnicity, comorbidities, dummy variables for calendar week, age (five-year bands), sex. Controls will be defined based on a negative test.

We will also construct a propensity score to be tested among those in the primary cohort and use this as an inverse propensity weight.

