We will assess vaccine waning looking for statistical evidence of reducing effectiveness, we will do a trend test on the period post-vaccination from 14-27 days onwards. We will also assess an exploratory change point from 28+, 42+, 56+ days to do a linear trend test post-vaccination.

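### Objective 5 asks whether waning differs by age group, sex and risk group, but section 5.1.4 plans only stratification, leaves out sex, and no between-group contrast of waning is pre-specified

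*SAP*

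**What the plan says.** The last objective in SAP section 2.2 is comparative: "Assess if waning of protection from booster dose differs by age group, sex and being in a high-risk COVID-19 group". Section 3.1 assigns a design to the first four objectives only; its last line reads "Objective c) and d) open prospective cohort study comparing outcomes amongst vaccinated people for differing lengths of time". The fifth has no design of its own.

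Section 5.1.4 carries the effect-modifier analysis under the words "Stratification into different population". It lists:
- primary schedule;
- age, as "Age group (18-49,50-64, 65+ years)";
- variant period;
- risk group, conditionally: "we will stratify analyses by COVID-19 risk group when data allow".

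Vaccine type and calendar time are also to be considered. Sex is not in the list. Elsewhere sex is an essential covariate (3.5), a descriptive breakdown (5.1.5, "including by age group and sex") and an adjustment variable (5.1.3, "We will consider adjusting for age, sex, socioeconomic position, geography and where possible, comorbidities").

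Section 5.1.5 defines the waning analysis: "We will assess vaccine waning looking for statistical evidence of reducing effectiveness", by a trend test over time since vaccination with exploratory change points. It does not mention subgroups. Section 6.1 bases interpretation on 95% confidence intervals, and section 5.1.6 declines any multiplicity correction.

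**The concern.** Whether waning differs between groups is a question about a difference between trends. Its answer is an estimate of that difference with an interval. Stratified models give each group's own result and stop there, and for sex the plan does not provide even that.

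Without a stated contrast, the reader of the results has separate stratum estimates and must compare them informally. An easy but faulty comparison is to note which groups show a significant trend and which do not. That depends on how much information each stratum holds as well as on how much protection wanes, so groups with the same waning can appear to differ. Conclusions of this kind could reach the vaccination advisory bodies named in section 6.2.

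**Working it through.** **Setting the sections side by side**

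| Modifier in Objective 5 | Listed in 5.1.4? | Between-group contrast of waning anywhere? |
| --- | --- | --- |
| Age group | Yes, three strata | No |
| Sex | No | No |
| High-risk group | Yes, if data allow | No |

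No interaction term, heterogeneity test, ratio of rate ratios or difference in slopes appears in the SAP.

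**How far informal comparison could mislead**

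The SAP gives no power, effect size or event count for this objective, so there is no planned figure to reproduce. What follows is an illustration. Inputs:
- Number of strata: three for age (5.1.4); two for sex, and two assumed for risk group.
- Two-sided 5% level, implied by the 95% intervals in 6.1.
- Within-stratum power p: an assumption, ranged from 50% to 95%.
- Identical true waning in every stratum, with independent strata.

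Probability that the strata disagree on significance:
- two strata: 2p(1 − p)
- three strata: 1 − p³ − (1 − p)³

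| p | Two strata | Three strata |
| --- | --- | --- |
| 0.95 | 2 × 0.95 × 0.05 = 9.5% | 1 − 0.8574 − 0.0001 = 14% |
| 0.90 | 2 × 0.90 × 0.10 = 18% | 1 − 0.729 − 0.001 = 27% |
| 0.80 | 2 × 0.80 × 0.20 = 32% | 1 − 0.512 − 0.008 = 48% |
| 0.50 | 2 × 0.50 × 0.50 = 50% | 1 − 0.125 − 0.125 = 75% |

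Unequal strata: suppose overall power is 90% and information splits 20/80 (both assumed). Stratum power is Φ((1.96 + 1.2816) × √share − 1.96), which gives 0.305 and 0.826. Discordance is 0.305 × 0.174 + 0.826 × 0.695 = 63%.

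A direct test of the time-since-booster by subgroup interaction at the 5% level errs in 5% of cases per modifier when waning is identical, whatever the stratum power.

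**What the contrast costs in precision**

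For two independent strata with log-RR slopes b₁ and b₂, the ratio of trend RRs is exp(b₁ − b₂), with standard error √(SE₁² + SE₂²) on the log scale. With equal standard errors this is √2 = 1.41 times a stratum's own standard error and twice that of the pooled slope. If the pooled trend has 90% power, a between-group difference as large as that trend would be detected with power Φ(3.2415/2 − 1.96) = 37%. A non-significant contrast must therefore not be read as evidence of equal waning.

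**The case against.** Four stronger readings are tempting, and the SAP does not support them.

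- **That discordant significance will be taken as effect modification.** No section says so. Section 6.1 points to confidence intervals, which can be read for estimate and width. The misreading is a risk left open by the lack of any comparison rule.
- **That every stratum gets its own trend test.** Section 5.1.5 does not tie the trend test to subgroups, and 5.1.4 does not mention trends. How trends are handled by subgroup is simply not stated.
- **That the difference cannot be estimated.** For age and risk group the strata are largely disjoint sets of people, so a difference and interval can be derived from stratum slopes if these are reported with their intervals. What is missing is pre-specification. A contrast chosen after the results are seen carries less weight.
- **That younger adults will have too few severe events.** The SAP gives no events by age. Section 3.6 gives only numbers boosted in Brazil, 10 million after ChAdOx1 and 5 million after BNT162b2, and these are not event counts. Power could be high in every stratum, in which case the lower end of the illustrated range applies.

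A further argument has merit: stratified models let confounder and calendar-week effects differ by group, whereas a single model with only one interaction term forces them to be common. That bears on how the contrast is obtained, not on whether one is needed.

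The omission of sex and the absence of any contrast both stand on the text.

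**Conclusion.** The point holds as a gap between a stated objective and its analysis. Objective 5 names three modifiers. One has no subgroup analysis, and none has a pre-specified estimate or interval for the difference in waning.

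The discordance figures of 9.5% to 50% (two strata) and 14% to 75% (three strata) show how unreliable an informal comparison could be. They rest on assumed stratum power, identical true waning and independent strata, and they apply only if strata are judged by significance. They do not predict what this study will find or how its authors will read it.

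The change should be made before analysis. It does not affect the main estimates for the other objectives.

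**What to change.** - Add sex to section 5.1.4.
- For age group, sex and risk group, pre-specify a contrast of the time-since-booster trend between subgroups, and report it as a ratio of trend RRs with 95% CI as the result for Objective 5. For the three age groups, name a reference group and add one joint test.
- Obtain the contrast from a time-since-booster by subgroup interaction, letting confounder and calendar-week effects vary by subgroup where needed, or equivalently from the difference in stratum-specific log-RR slopes.
- State, or cite, the definition of the risk group that the contrast uses.
- Keep the stratum estimates as description, and say that differences in significance between strata will not be interpreted.

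Cost: SAP wording and one contrast per modifier, repeated by primary schedule, country and outcome. For the primary outcome this is 3 modifiers × 2 schedules × 2 countries = 12. No new data are needed. The contrasts will be less precise than the stratum estimates, and the SAP should say so.

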### 5.1.5 Analytical techniques

We will commence analysis by conducting descriptive analyses to visually inspect trends in vaccination delivery, age-specific COVID-19 hospitalisations and COVID-19 deaths, including by age group and sex. This will include checking the number of people who have received two doses and the length of follow-up available following the second dose by vaccine type. Including plotting Lexis diagram to afford for the correlated structure of the data (Calendar Time/Length of Follow-up)

For the analysis consisting of individuals with at least two doses, we will stratify the cohort based on the month of the second dose of each individual. The vaccination status will be classified as:

- Second dose:
  - <2 weeks
  - 2-9 weeks
  - 10-19 weeks
  - ≥20 weeks without a booster dose [Reference Period]
- Booster dose:
  - <2 week
  - 2-4 weeks
  - 5-8 weeks
  - 9-12 weeks
  - ≥13 weeks

This variable will be used to fit a Poisson regression to obtain rate ratios (RRs) and their 95% confidence intervals (CIs). If we observe overdispersion, we will consider using Negative Binomial regression models or Poisson with robust standard errors. Models will be adjusted for the relevant confounders above, including a set of dummy variables for calendar week.

The models will be fit to a dataset with all events and a random sample, without replacement, of 100 individuals per event (for hospitalisation and death, 10 for positive tests). The sample weights will be calculated to represent the sampling fraction, thus ensuring the correct calculation of the person-years at risk for the whole population.

The primary analysis for the test negative will be on individuals who are symptomatic at the time of test and the date of symptom onset is 0-10 days before the test. We will then establish the number of weeks post-vaccination for the cases and controls calculated as time between sample collection date and vaccine dose. The odds' ratio will be calculated using a logistic regression. Adjusted for: race/ethnicity, comorbidities, dummy variables for calendar week, age (five-year bands), sex. Controls will be defined based on a negative test.

We will also construct a propensity score to be tested among those in the primary cohort and use this as an inverse propensity weight.

We will assess vaccine waning looking for statistical evidence of reducing effectiveness, we will do a trend test on the period post-vaccination from 14-27 days onwards. We will also assess an exploratory change point from 28+, 42+, 56+ days to do a linear trend test post-vaccination.

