## 3.5 Inclusion/exclusion criteria

Inclusion criteria for the primary cohort:

- Receive at least two doses of BNT162b2 or ChAdOx1 before or during the study period.

Exclusion criteria for the primary cohort:

- Inconsistent vaccination records (i.e. received a second dose with no record of a first dose, received doses from different vaccine types or interval between doses of less than 14 days)
- Missing essential covariates (sex, age, geography)
- Children (under the age of 18 years)
- Hospitalization previous to the study start date
- A positive test within 28 days of the study start date

Inclusion criteria for the TND:

- Receive at least two doses of BNT162b2 or ChAdOx1 at the sample collection date.

Exclusion criteria for the TND:

- Tests within 90 days of a previous positive test
- Negative tests followed by a positive test within 7 days
- Negative tests within 14 days of a previous negative test
- Missing essential covariates (sex, age, geography)
- Children (under the age of 18 years)

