## 3.6 Sample size calculations

Based on a preliminary review of descriptive statistics in both countries, we anticipate the following numbers:

- Scotland:
  - ChAdOx1:
  - BNT162b2:
- Brazil
  - ChAdOx1: 10 million individuals with booster from 49M with 2 doses
  - BNT162b2: 5 million individuals with booster from 28M with 2 doses

If adequate numbers are not available for statistical analysis for a specific vaccine, we will not progress that analysis and censor individuals who receive that vaccine.

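### Robust standard errors in the cohort Poisson models are made to depend on overdispersion, although the need for them comes from the sampling and inverse propensity weights

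*SAP*

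**What the plan says.** All of the cohort modelling is in SAP section 5.1.5.

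- Model: "This variable will be used to fit a Poisson regression to obtain rate ratios (RRs) and their 95% confidence intervals (CIs".
- Data: all events plus "a random sample, without replacement, of 100 individuals per event (for hospitalisation and death, 10 for positive tests".
- Weights: "The sample weights will be calculated to represent the sampling fraction, thus ensuring the correct calculation of the person-years at risk". Correct person-time is the only purpose given, and no variance method is attached.
- Second weight: "We will also construct a propensity score to be tested among those in the primary cohort and use this as an inverse propensity weight". Again no variance method is given, nor whether the weights are stabilised.
- Robust variance: "If we observe overdispersion, we will consider using Negative Binomial regression models or Poisson with robust standard errors". The section does not say how overdispersion is measured, on person-level rows or aggregated cells, or with or without the weights.

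Section 6.1 interprets associations on their 95% confidence intervals.

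For the test-negative design, 5.1.5 names a logistic regression. Among the exclusions in 3.5 is "Negative tests within 14 days of a previous negative test", together with tests within 90 days of a positive and negatives followed by a positive within 7 days. Section 4.2 keeps earlier positives at 91-180 and over 180 days as covariate levels.

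**The concern.** A weighted Poisson fit with ordinary standard errors treats a sampled person of weight 10 as ten observed people. The point estimate is sound, but the standard error is that of the full cohort and leaves out the variance added by sampling. Inverse propensity weights raise the same problem, usually more strongly. Both call for a sandwich or design-based variance from the outset.

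The plan instead lets a dispersion statistic decide, and then only as something to consider. That statistic does not measure the problem, and one of the two remedies does not cure it. At stake is whether the 95% intervals on which 6.1 relies have their stated coverage, and whether the variance estimator is settled before the data are seen.

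**Working it through.** The SAP gives no event counts, dispersion value or standard error, so there is no planned figure to reproduce. The inputs from the SAP are the ratios of 100 and 10 individuals per event and the Brazilian cohort sizes in 3.6 (for example "ChAdOx1: 10 million individuals with booster from 49M with 2 doses"; 28 million for BNT162b2). All else is assumed.

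**1. Plausible sampling weights.** With N people, D events and k sampled per event, w = (N − D)/(kD).
- Assuming 10,000 to 100,000 severe events and k = 100: for 49 million, (49,000,000 − 10,000)/(100 × 10,000) = 49.0, falling to 4.9; for 28 million, 28 to 2.8.
- Assuming 200,000 to 1,000,000 infections and k = 10: 24 to 4.8, and 14 to 2.7.

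**2. What the Pearson check returns.** With 0/1 records the weighted Pearson sum is about N + D over about (k + 1)D records. Since N = wkD + D, dispersion ≈ (wk + 2)/(k + 1), which is close to w. For k = 100 and w = 6.52: (652 + 2)/101 = 6.48. For k = 10 and w = 25.62: (256.2 + 2)/11 = 23.5.

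This was simulated with no extra-Poisson variation: 40,000 people, ten weekly rows, rate ratio 0.4, 60 replicates at k = 100 and 150 at k = 10. The SE columns refer to the log rate ratio in the weighted sample.

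| k | w | Pearson/df, full cohort | Pearson/df, weighted sample | Ordinary SE | Sandwich SE |
|---|---|---|---|---|---|
| 100 | 6.52 | 1.00 | 6.50 | 0.3641 | 0.3648 |
| 10 | 25.62 | 1.00 | 24.46 | 0.2311 | 0.2356 |
| 10 | 6.42 | 1.00 | 6.14 | 0.1149 | 0.1169 |
| 10 | 2.53 | 1.00 | 2.45 | 0.0728 | 0.0736 |

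The choice of statistic also matters: a separate run with w = 15.0 at k = 100 gave Pearson dispersion 14.8 but deviance dispersion 0.14. With the same kind of data aggregated into cells and sampled person-time as offset, Pearson/df was 1.02 (k = 100) and 1.10 (k = 10).

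**3. Error from the sampling weights alone.** A rough formula for the true over the ordinary SE is sqrt(1 + 1/k).
- k = 100: sqrt(1.01) = 1.005; a nominal 95% interval covers 94.9%.
- k = 10: sqrt(1.1) = 1.049; coverage 93.8%.

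In the table, sandwich over ordinary is 0.3648/0.3641 = 1.002 at k = 100, and 1.019, 1.017 and 1.011 at k = 10. Two other simulations at k = 10 compared the ordinary SE with the empirical one: 0.1065 against 0.1105 (3.6% too small; sandwich 0.1112) and 0.0938 against 0.0992 (5.4% too small; sandwich 0.0987).

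**4. Whether a Negative Binomial model helps.** In one simulated row-level sample, the weighted log-likelihood was highest at dispersion near zero (−4335.85, against −4336.70 at dispersion 1). The ordinary SE stayed at 0.1271 over that range.

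**5. Inverse propensity weights.** Assumed: rate ratio 0.4, about 1% event risk, 10 per event, moderate confounding, no extra-Poisson variation, 300 replicates.
- Unstabilised: ordinary SE 0.077 against empirical 0.144 to 0.157, a ratio of 0.53 to 0.49. A 95% interval built on half the true SE covers 2Φ(1.96 × 0.5) − 1 = 67%. Simulated coverage was 67-71%, against 94-96% with the sandwich.
- Stabilised: ordinary SE 6-8% too small, coverage 93%.

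Part of the first result is structural: unstabilised weights for two exposure groups average about 2, so the model acts as if the cohort were twice its size.

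**6. Test-negative design.** The exclusions remove only closely spaced tests, so a person can enter more than once. Take a design effect of 1 + (m − 1)ρ, with m tests per person and ρ the effective within-person correlation. Assuming m = 1.1 to 1.5 and ρ = 0.05 to 0.3, the SE should be larger by sqrt(1.005) to sqrt(1.15), that is 0.3% to 7.2%. The SAP supplies neither m nor ρ.

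**The case against.** Four points can be made for the plan.

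- **Small effect on the primary outcome.** At 100 per event the sampling weights cost at most about 0.5% of the SE. The larger figure applies to infection, which 5.1.2 already treats as more tentative. This stands. A reader might infer that the primary intervals are unreliable because they rest on an artefact. The documents do not support that for the sampling weights.
- **No damaging branch.** If the inflated check fires, one remedy is the appropriate variance and the other leaves the SE where it was. Rescaling by the Pearson statistic would inflate SEs about 1.6- to 4.9-fold (square roots of 2.45 and 24.46), but the SAP does not offer it. This stands, yet a correct variance reached by accident is not a specified one, and the Negative Binomial branch still omits the sampling variance.
- **The inflated check needs weighted row-level data.** The SAP does not fix the layout, and its references to rates and person-years fit aggregated cells equally well. This stands too. In that layout the check would probably stay silent and the sampling variance would go unaddressed, so the rule is unsuitable either way. It does not follow that a dispersion check is illegitimate; on aggregated counts it is a fair diagnostic.
- **The test-negative point is inferred from silence.** Naming logistic regression does not exclude clustered standard errors. Exposure changes between a person's tests, and if earlier infection protects, outcome correlation could be negative. This stands: a reader might infer materially narrow intervals there, but no such size can be derived from the SAP.

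**Conclusion.** The point holds as one about the rule that selects the variance. The sampling and inverse propensity weights require a robust or design-based variance; overdispersion is a separate matter, the check for it depends on an unstated layout and statistic, and a Negative Binomial model is no remedy for sampling variance.

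The size differs by weight. Sampling weights alone matter little for hospitalisation and death and modestly for infection. The material risk lies with the propensity-weighted analysis if the weights are unstabilised: coverage near 70% is possible, but that figure depends wholly on the assumed confounding and event risk, and the SAP describes that analysis as one to be tested. The simulations drew the sample from people without events and used few replicates, so their SE and dispersion ratios are firmer than their coverage figures. Repeat tests in the test-negative model are a secondary precaution of unknown size.

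**What to change.** In 5.1.5, replace the conditional sentence with an unconditional one: every Poisson model fitted to the sampled data or using inverse propensity weights will report sandwich standard errors clustered on the person, or a design-based equivalent that reflects the sampling, regardless of any dispersion statistic. If data are aggregated for fitting, keep the person identifier so that this variance can be computed. Say whether the propensity weights are stabilised.

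The overdispersion check may stay as a descriptive diagnostic, with its statistic, data layout and use of weights stated.

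For the test-negative logistic model, add person-clustered standard errors.

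The cost is a few sentences in the SAP and about one line of code per model. Intervals become slightly wider in most analyses, and appreciably wider only where the ordinary ones would have been misleading.

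### The cohort model gives every age the same calendar-week curve, so age differences in epidemic timing can mimic or hide waning after the booster

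*SAP*

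**What the plan says.** - **Cohort Poisson model (SAP 5.1.5):** "Models will be adjusted for the relevant confounders above, including a set of dummy variables for calendar week". Section 5.1.3 supplies the age term. For Brazil it reads "In Brazil, we anticipate adjusting for age (five-year bands), sex, the primary reason for vaccination, race/ethnicity and calendar week"; for Scotland, "we anticipate adjusting for the following confounders in Scotland: age (five-year bands". No interaction of age with calendar week or with booster band is named.
- **Test-negative logistic model (5.1.5):** "Adjusted for: race/ethnicity, comorbidities, dummy variables for calendar week, age (five-year bands), sex". Again no interaction is named.
- **Waning test (end of 5.1.5):** "we will do a trend test on the period post-vaccination from 14-27 days onwards". The text does not say whether this is done over all ages or within age groups.
- **Age strata (5.1.4):** "Age group (18-49,50-64, 65+ years" is listed among the populations for stratification, together with variant period. The fifth objective in 2.2 asks whether waning differs by age group.
- **Month of second dose (5.1.5):** the cohort is stratified by this month, but the SAP does not say whether that means added dummies, separate week effects or separate models.

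**The concern.** The study asks whether the RR rises with time since booster. With age and week as main effects only, the model assumes that the log rate is age effect + week effect + band effect. Suppose the true log rate also holds a departure d(age, week), because waves reach age groups at different times. The model can then express d only through the band coefficients, to the extent that bands remain associated with age and week jointly.

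That association is strong when boosters are offered by age. The ≥13-week band then holds mostly the ages boosted first, and in the later weeks. A flat booster effect can come out as a slope, and a true slope can be flattened. A booster effect that differs by age acts in a similar way in a pooled model. With the millions of boosted people anticipated in 3.6, narrow intervals would not reveal such a bias.

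**Working it through.** The SAP gives no power, alpha, event count or roll-out schedule bearing on this point, so there is no planned figure to reproduce. The check fits Poisson models with a person-time offset to expected counts (no sampling noise), with the booster RR held constant from 2 weeks on. The true ratio of the ≥13-week RR to the 2-4-week RR is therefore 1.00.

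**From the SAP.** The vaccination-status bands, the reference period and the three age groups come from 5.1.4 and 5.1.5. The footnote to 5.1.3 gives the age bands: 18-24, thirteen bands from 25-29 to 85-89, and 90+, so 1 + 13 + 1 = 15. The 18-49 group holds 6 of them, 50-64 holds 3 and 65+ holds 6.

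**Check 1: shifted waves (all inputs assumed).** 26 weeks; booster start staged from week 1 (oldest) to week 14 (youngest); 25% weekly uptake towards an 80% cap; a Gaussian wave with SD 3 weeks and 5-fold peak at week 17 in the youngest, reaching the oldest 1, 2 or 3 weeks later. Infection: flat baseline risk by age, true RR 0.60. Severe outcome: rate rising 0.35 log units per band, true RR 0.30.
- Infection, main effects: ratios 1.07, 1.11 and 1.14. With a 2-week offset reversed (oldest peak first): 0.83. With no offset: 1.00.
- Infection, age-group-by-week terms: 1.01, and 0.97 for the reversed offset.
- Severe, main effects: 0.98 to 1.00.
- Within the 18-49 stratum, main effects: 1.04 to 1.14 (infection) and 1.03 to 1.09 (severe). The two older strata are nearly clean.

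Other choices for inputs not fixed by this description moved the infection ratio over 1.06 to 1.26 and the severe ratio over 0.95 to 1.05 for the same offsets.

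**Check 2: steady drift (all inputs assumed).** 5 age bands; 30 weeks; median booster week 1, 4, 8, 11 and 14 from oldest to youngest; 80% boosted. The log rate drifts over time by a coefficient s per age step; positive s moves incidence towards older ages. Here s is a sensitivity parameter, not an estimate.

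| Main-effects model | 2-4 wk | 5-8 | 9-12 | ≥13 | Ratio ≥13 / 2-4 |
|---|---|---|---|---|---|
| Severe, true 0.30, s = +0.15 | 0.291 | 0.291 | 0.294 | 0.309 | 0.309/0.291 = 1.06 |
| s = +0.3 | 0.282 | 0.281 | 0.287 | 0.316 | 0.316/0.282 = 1.12 |
| s = +0.5 | 0.270 | 0.267 | 0.275 | 0.322 | 0.322/0.270 = 1.19 |
| s = -0.3 | 0.315 | 0.315 | 0.308 | 0.278 | 0.278/0.315 = 0.88 |
| Infection, true 0.50, s = +0.3 | 0.475 | 0.473 | 0.482 | 0.594 | 0.594/0.475 = 1.25 |
| s = -0.3 | 0.533 | 0.537 | 0.529 | 0.433 | 0.433/0.533 = 0.81 |

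Age-by-week terms return 0.30 or 0.50 in every band. Within 18-49 the main-effects ratio is 0.319/0.301 = 1.06 (severe, s = +0.3), 0.336/0.304 = 1.11 (severe, s = +0.5) and 0.542/0.501 = 1.08 (infection, s = +0.3). For severe at s = -0.3 it is 0.286/0.302 = 0.95. Within 65+ it is 0.302/0.294 = 1.03 (severe, s = +0.3). The 50-64 group is a single band here, so it is flat by construction. Over all runs with incidence shifting towards older ages, the 18-49 residual is about 1.04 to 1.17.

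**Check 3: booster effect differs by age, same timing.** In the set-up of check 2, with severe RR 0.20 (youngest) to 0.45 (oldest), main effects give 0.409/0.381 = 1.07. The opposite gradient gives 0.226/0.245 = 0.92. Age-by-week terms alone leave 0.401/0.389 = 1.03 in the first case. The SAP's strata give 0.236/0.231 = 1.02 (18-49), 1.00 (50-64) and 0.423/0.414 = 1.02 (65+). In the set-up of check 1, with RR 0.25 at 18-49 and 0.33 to 0.45 at 65+, the pooled ratio was 1.04 to 1.19 depending on open inputs. It was exactly 1.00 in every stratum when the RR was constant within each group.

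**Month of second dose.** In the set-up of check 2 with s = +0.15, month dummies barely help: 0.308/0.292 = 1.05 against 1.06. Separate week effects per month can help: in a run with incidence shifting to the young, the RRs went from 0.302 to 0.298, against 0.308 to 0.290 for main effects. This rests on how closely month tracks age, and the bias was not removed uniformly.

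**The case against.** Most of the case on the other side stands.

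- **Age is not handled by main effects alone.** Fitting within the three groups of 5.1.4 lets week effects and band RRs differ by group. That removes most of the timing bias and nearly all the bias from an age-dependent booster effect. It does not clear the 18-49 group, which spans six bands, and the strata are listed as effect-modifier analyses with no statement that the headline result comes from them.
- **The trend test is not stated to be all-age.** A reader might infer that it is pooled and criticise it on that basis. The text is silent, so the fair point is that this must be stated.
- **The largest ratios concern infection.** Section 5.1.2 makes hospitalisation or death primary and treats infection results with more caution. For the severe outcome under 1- to 3-week offsets the shift is small.
- **The direction is not fixed.** A reader might infer that the omission manufactures waning. Reversing the offset or the drift hides waning instead, and the SAP has no data to choose between these cases.
- **Other planned features were not modelled:** variant-period strata, propensity weighting and the Lexis diagram. The wording of 5.1.3 is also tentative and does not exclude interactions.
- **The test-negative model was not simulated.** Its bias depends on how the case-to-control ratio varies by age and week, so the cohort figures cannot be carried over to it.

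**Conclusion.** The point holds in a limited form. The cohort model as written has no age-by-week term. Under age-staged uptake and age-specific epidemic timing, both assumed, the time-since-booster RRs can drift in either direction without any true change in protection. The effect is material for infection, and negligible to moderate for the primary composite. The documents do not support a claim that the primary result is seriously biased, or that any waning found would be an artefact. What remains after the SAP's own stratification is the residual inside 18-49 and the unstated choice between pooled and stratified headline results. The change is worth making because it protects the study's central estimate at little cost.

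**What to change.** In 5.1.5:

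1. State whether the headline RRs and the trend test are pooled over age or come from the age strata.
2. In the cohort Poisson model, replace the common week dummies by age-group-by-calendar-week effects, or by age-specific smooths of calendar time in mgcv, which 5.3 already lists. Use finer age groups within the 18-49 stratum.
3. If the headline RRs or trend test are pooled, add a boosted-by-age-group term so that the slope across bands is estimated within age. Age-by-week terms alone do not deal with a booster effect that differs by age.
4. Say how month of second dose enters the model.
5. Keep the main-effects model as a sensitivity analysis, and fit the age-by-week term in the test-negative logistic model as a parallel check.

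The cost is a few lines of text, slightly wider intervals, and sparse cells for deaths at younger ages, which smooths or coarser groups can handle. No new data are needed.
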